## Abstract

**Aims:**

The primary aim of this study is to quantify and compare outcomes following a dorsally displaced fracture of the distal radius in elderly patients (aged ≥ 65 years) who are managed conservatively versus with surgical fixation (open reduction and internal fixation). Secondary aims are to assess and compare upper limb-specific function, health-related quality of life, wrist pain, complications, grip strength, range of motion, radiological parameters, healthcare resource use, and cost-effectiveness between the groups.

**Methods:**

A prospectively registered (ISRCTN95922938) randomized parallel group trial will be conducted. Elderly patients meeting the inclusion criteria with a dorsally displaced distal radius facture will be randomized (1:1 ratio) to either conservative management (cast without further manipulation) or surgery. Patients will be assessed at six, 12, 26 weeks, and 52 weeks post intervention. The primary outcome measure and endpoint will be the Patient-Rated Wrist Evaluation (PRWE) at 52 weeks. In addition, the abbreviated version of the Disabilities of Arm, Shoulder and Hand questionnaire (QuickDASH), EuroQol five-dimension questionnaire, pain score (visual analogue scale 1 to 10), complications, grip strength (dynamometer), range of motion (goniometer), and radiological assessments will be undertaken. A cost-utility analysis will be performed to assess the cost-effectiveness of surgery. We aim to recruit 89 subjects per arm (total sample size 178).

**Discussion:**

The results of this study will help guide treatment of dorsally displaced distal radial fractures in the elderly and assess whether surgery offers functional benefit to patients. This is an important finding, as the number of elderly distal radial fractures is estimated to increase in the future due to the ageing population. Evidence-based management strategies are therefore required to ensure the best outcome for the patient and to optimize the use of increasingly scarce healthcare resources.

Cite this article: *Bone Jt Open* 2024;5(10):920–928.

**Primary aim** To undertake a single-centre parallel group randomized controlled trial to compare surgical fixation to conservative management for displaced distal radius fractures in the elderly (aged ≥ 65 years) based on functional outcome assessed using the PRWE at 52 weeks
**Secondary aims** To measure function assessed using the PRWE at other timepoints (six, 12, and 26 weeks) To measure function assessed using QuickDASH at six, 12, 26, and 52 weeks. To investigate health-related quality-of-life using EQ-5D-3L at six, 12, 26, and 52 weeks To measure pain using VAS pain score at six, 12, 26, and 52 weeks To compare complication rates at 52 weeks To compare grip strength and range of motion at 12 weeks To compare radiological parameters, including union and malunion To investigate, using appropriate statistical and economic analysis methods, the healthcare resource use, and comparative cost-effectiveness at one year (52 weeks)

EQ-5D-3L, EuroQol five-dimension three-level questionnaire; PRWE, Patient-Rated Wrist Evaluation; QuickDASH, abbreviated version of Disabilities of Arm, Shoulder and Hand questionnaire.

## Methods

### Trial design

A single-centre prospective randomized RCT with parallel groups allocated in a 1:1 ratio will be undertaken. The trial was registered with the International Standard Randomized Controlled Trial Number Registry (ISRCTN) as ISRCTN95922938 on 3 December 2021.

### Study participants

Adults aged 65 years and older with an isolated dorsally displaced fracture of the distal radius.

### Study setting

Patients will be recruited from the orthopaedic department of a major academic trauma centre within the UK.

### Eligibility criteria

The eligibility criteria are detailed in Table II. Patients must fulfil all eligibility criteria, and this will be assessed by a member of the research team prior to approaching patients to consider participation in the study. It is commonplace in the study centre for patients presenting with a displaced distal radius fracture to undergo closed reduction under Bier’s block in the emergency department (ED). However, if a patient with a displaced fracture has not undergone a Bier’s block in the ED, they would still be eligible for the trial if they meet the necessary criteria.

**Table II. T2:** Study inclusion and exclusion criteria.

**Inclusion criteria** Aged ≥ 65 years Dorsally angulated fracture of the distal radius The treating surgeon believes the patient is suitable for surgical fixation Operation date within three weeks of fracture Closed or Gustilo-Anderson grade I injury
**Exclusion criteria** Patients unable to give informed consent Patients medically unfit to undergo surgery Volar displaced fractures Partial articular and isolated radial styloid fractures Associated fractures to the upper limb and/or pre-existing pathology adversely affecting function Associated ligamentous injury, dislocation, or subluxation of the wrist Open fractures of Gustilo-Anderson grade II or higher Persisting neurovascular deficit requiring operative intervention Off-ended/severely displaced fractures post attempted reduction that are deemed to required surgery by the treating surgeon Patients who are non-resident locally and will be unable to attend for local follow-up Patients unable to comply with follow-up, including English-language patient-reported outcome measures, either on the telephone or by post

A displaced fracture will be defined as one or more of:^25^

Carpal malalignment (defined as the displacement on a lateral view of the longitudinal axis of the capitate dorsal to the longitudinal axis of the radius).Dorsal angulation of greater than 10° from the anatomical position.Radial shortening of more than 2 mm.Intra-articular step of more than 2 mm.Intra-articular gap of more than 5 mm.

## Interventions

### Conservative management

Patients randomized to the conservative arm will complete a total of six weeks in a below-elbow cast. This is routinely an initial below-elbow plaster of Paris Colles (dorsal, below-elbow) backslab, although some patients do undergo initial circumferential synthetic Colles casting. If a backslab is applied, this is completed with circumferential synthetic cast material at one week post injury, followed by change to a circumferential synthetic Colles cast at two weeks post injury.

### Surgical fixation

Patients randomized to the operative arm will undergo a one-off surgical procedure carried out on a day-case basis. This will be in the form of a volar locked plate. Following surgery, the postoperative assessment and course will be as per routine protocol for patients in the treating centre. The provision of a removable splint will be as per standard care, at the discretion of the treating surgeon.

### Rehab/physiotherapy

Physiotherapy will be arranged as required as per standard care.

## Outcome measures

### Primary outcome measure

The primary outcome measure is the PRWE at 52 weeks post intervention.^24^ The PRWE assesses wrist function using 15 questions (rated 0 to 10) based on the patient’s pain (five questions) and disability (ten questions) to produce a score from 0 (no disability) to 100 (maximum disability).

### Secondary outcome measures

The secondary outcome measures are detailed below:

Abbreviated version of the Disabilities of Arm, Shoulder and Hand (QuickDASH) questionnaire:^26^ an 11-question upper-limb-specific validated measure of disability with the outcome score ranging from 0 (no disability) to 100 (maximum disability), with optional work and sport/musical instrument modules.^27^EuroQol five-dimension three-level questionnaire (EQ-5D-3L): to measure health-related quality of life (HRQoL).Visual analogue scale (VAS) pain score (visual scale 1 to 10): to measure participant’s pain.Complications: occurrence will be determined at each assessment point and include complex regional pain syndrome (CRPS), diagnosed using the Budapest Criteria,^28,29^ nerve injury, tendon injury, infection, and reoperation rates.Grip strength: measured with a dynamometer and compared with the uninjured side and adjusted for hand dominance.ROM at the wrist: measured using a standard full-circle goniometer. Flexion, extension, supination, and pronation will be measured and compared with the uninjured side.Radiological assessment: pre- and post-intervention standard posteroanterior and lateral radiographs of the wrist will be used. Radial inclination, radial height, ulnar variance, palmar tilt, intra-articular gap, and intra-articular step will be measured. The presence or absence of carpal malalignment, volar hook,^30^ dorsal comminution, and volar comminution will be assessed in addition to the AO/Orthopaedic Trauma Association (AO/OTA),^31^ Zenke,^26^ and Buttazzoni classifications of the fracture.^32^ Outcome will also be assessed in detail with regards to fracture position on healing, complications, union, and the development of radiological degenerative changes.Healthcare resource use and cost-effectiveness including return to work.

### Participant timeline

The schedule of assessments is detailed in Figure 1. In addition to patient demographics, data will also be collected on patent frailty in the form of a clinician-assessed score, the Clinical Frailty Score,^33^ and a patient-assessed score, the Program of Research to Integrate the Services for the Maintenance of Autonomy-7 (PRISMA-7).^34^ Longer-term follow-up will be carried out in the form of postal surveys at 26 weeks and 52 weeks (primary endpoint). This both minimizes inconvenience to the patient and reduces the need for face-to-face appointments.

**Fig. 1 F1:**
[figure not shown]
SPIRIT figure for the eFORRCE study.

### Sample size

A total sample size of 142 subjects (71 in each group) is required to detect a difference in mean PWRE scores between groups of 11, assuming a common standard deviation of 20 using a two-sided, two-sample test with 5% significance and 90% power.^35^ To account for a loss to follow-up rate of 20% at 52 weeks, this has been increased to 178 patients (89 per group).

### Participant recruitment

Patients will be recruited from the ED, orthopaedic outpatient clinic, or an inpatient ward. The method by which they will be identified will vary based on where they are recruited from. The treating team in any of these settings will introduce the study, provide the patient with an information sheet, and ensure the research team are informed. A clinical member of the research team will then determine whether or not the patient fits the inclusion/exclusion criteria, explain the trial, answer questions, and begin the informed consent process if the patient wishes to proceed. Recruitment commenced on 7 February 2022.

### Randomization/treatment allocation

After informed consent has been obtained and baseline information collected, participants will be randomly allocated to receive either conservative management in a cast or surgical fixation. An independent statistician generated a randomization schedule using block randomization with a random block size to allocate participants in a 1:1 ratio stratified by fracture AO/OTA classification (type A, type C) to ensure as far as possible equal numbers of each fracture type in each group. A member of staff independent of the study used this schedule to create a series of sequentially numbered opaque sealed envelopes containing the treatment allocation as specified by the statistician.

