## Data management

### Statistical analysis plan

Where variables are continuous, descriptive statistics will be presented and this will provide number of observations, number of missing observations, mean (SD), median (IQR), maximum, and minimum values. Where variables are categorical, we will present the number and % of each treatment arm.

Comparison of PWRE at 12 months (primary outcome) between treatment arms will be analyzed using a paired *t*-test. Descriptive analysis of measures at each timepoint will be presented split by treatment arm, and comparisons will be made in a similar way to the primary outcome. Grip strength and ROM at 12 weeks will be corrected using the non-affected side, and then comparison of the corrected values will be made between treatment arms using a paired *t*-test.

The comparison of complication rate and radiological success will be made between treatment arms using a binomial test for the comparison of proportions, and we will present the difference in percentage between groups accompanied by the 95% CI for the difference and p-value associated with the comparison.

For time to return to work and sports, we will analyze this using a Kaplan-Meier survival curve and present this along with the log-rank statistic comparing the two treatment arms. We will also present a breakdown of the number of dropouts by treatment arm and, if appropriate, compare this rate using a binomial test for the comparison of proportions.

The sample size calculation accounts for a 20% loss to follow-up rate. Analysis will be on an intention-to-treat basis. Per protocol and as treated analyses will also be undertaken for the primary outcome only.

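### Randomisation is stratified by AO/OTA type, but the stated PRWE, complication, radiological and return-to-work/sports comparisons ignore the stratum: a small, conservative loss of precision if type is prognostic

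*Protocol article*

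**What the plan says.** The section on randomisation and treatment allocation describes random-length blocks used to "allocate participants in a 1:1 ratio stratified by fracture AO/OTA classification (type A, type C". AO/OTA type is the only stratification factor named.

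The Statistical analysis plan section names the tests:

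- **Primary outcome:** "Comparison of PWRE at 12 months (primary outcome) between treatment arms will be analyzed using a paired *t*-test".
- **Measures at each timepoint:** "comparisons will be made in a similar way to the primary outcome".
- **Grip strength and range of motion:** "Grip strength and ROM at 12 weeks will be corrected using the non-affected side", followed by a t-test between arms. Secondary outcome measures adds that grip strength is "compared with the uninjured side and adjusted for hand dominance".
- **Complications and radiological success:** compared "using a binomial test for the comparison of proportions, and we will present the difference in percentage between groups".
- **Return to work and sports:** a Kaplan-Meier curve; the authors will "present this along with the log-rank statistic comparing the two treatment arms".

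None of these statements brings in AO/OTA type. The Sample size section likewise assumes a two-sample test without adjustment. On other baseline data, the Participant timeline section says that, besides demographics, "data will also be collected on patent frailty in the form of a clinician-assessed score, the Clinical Frailty Score", together with a patient-assessed frailty score.

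**The concern.** Blocking within fracture type makes the two arms nearly equal in their mix of types A and C. Chance imbalance in type therefore adds almost nothing to the true sampling variance of the treatment difference. An unadjusted t-test does not know this: its pooled SD still includes the variation between types. If type predicts the outcome, the reported standard error exceeds the true one, confidence intervals are a little wide, and the actual type I error falls below 5%. The same reasoning applies in kind to the unstratified test of proportions and the log-rank test.

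What is at stake is precision, not validity. The design balances on fracture type, and the stated analyses do not take up the gain that this makes available.

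Age and frailty are a different matter. They did not enter the randomisation, so omitting them leaves the standard error valid. Adjusting for them could only improve efficiency.

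**Working it through.** **Inputs from the protocol article (Sample size):** difference 11, SD 20, two-sided 5%, 90% power, 71 per arm evaluable, 20% loss, 89 per arm randomised.

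**Assumptions, because the documents give no figure:** the SD of 20 is the total SD, including variation between types; types A and C differ by D points in 52-week PRWE, with D from 2 to 10; the share p of one type is 0.3 to 0.5.

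**Step 1. The plan's own figure.** The two-sample t solution is 70.44, so 71 per arm and 142 in total. Dividing by 0.8 gives 142/0.8 = 177.5, so 178. Both stated figures are reproduced. Power at 71 per arm is 90.2% (t) or 90.6% (normal approximation).

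**Step 2. Share of variance due to the stratum.** R² = p(1 − p)D²/20².

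- Smallest case (p = 0.3, D = 2): 0.21 × 4/400 = 0.0021.
- Largest case (p = 0.5, D = 10): 0.25 × 100/400 = 0.0625.

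**Step 3. Standard error and type I error.** The unadjusted SE is 20 × √(2/71) = 3.357. The SE with the stratum in the model is 3.357 × √(1 − R²). The excess is 1/√(1 − R²) − 1. The actual type I error of the unadjusted test is 2[1 − Φ(1.96/√(1 − R²))].

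**Step 4. Power of the adjusted analysis at 71 per arm.** Normal approximation: Φ(11/SE − 1.96). The t column uses the noncentral t distribution with the same SE.

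| Case | R² | Adjusted SE | Unadjusted SE too large by | Type I error, unadjusted | Power, normal | Power, t |
|---|---|---|---|---|---|---|
| Type not prognostic | 0 | 3.357 | 0% | 5.0% | 90.6% | 90.2% |
| D = 2, p = 0.3 | 0.0021 | 3.353 | 0.1% | 5.0% | 90.7% | 90.3% |
| D = 5, p = 0.5 | 0.0156 | 3.330 | 0.8% | 4.8% | 91.0% | 90.7% |
| D = 10, p = 0.5 | 0.0625 | 3.250 | 3.3% | 4.3% | 92.3% | 91.9% |

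**Step 5. Simulation check** (142 patients, equal shares of types, allocation balanced within type, 10,000 runs per scenario).

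- No type difference: mean unadjusted SE 3.35 against a true SD of the estimate of 3.34; type I error 4.8%.
- 10-point type difference: SE 3.35 against a true 3.25; type I error 4.2% unadjusted and 4.9% adjusted; power 90.6% unadjusted and 91.6% adjusted.

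The Monte Carlo standard error is about 0.2 percentage points for type I error (√(0.05 × 0.95/10,000)) and 0.3 for power (√(0.9 × 0.1/10,000)). The simulation therefore supports the direction and approximate size.

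**Step 6. Adding baseline covariates.** Suppose that stratum, age and frailty together explain 10% or 20% of the variance (assumption). The residual SD is 20 × √0.9 = 18.97 or 20 × √0.8 = 17.89, and the SE is 3.184 or 3.002. Power by the t calculation is then 92.9% or 95.3%, against 90.2% unadjusted. The part of this gain that comes from age and frailty is efficiency only and corrects no error.

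**The case against.** The strongest reply is that nothing invalid is planned. The sample size was computed for an unadjusted test, it is reproduced exactly, and its 90% power is met without adjustment. Type I error is not inflated and the estimate is unbiased. Whether there is any loss depends on AO/OTA type being prognostic, which the documents do not show; if it is not, the unadjusted standard error is correct. All of this stands, and it limits the size of the point.

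It could also be said that covariates are usually settled in a separate analysis plan. For age and frailty that is fair. It is weaker for the stratum: the article names the tests, and a plain t-test has no place for a stratum, so a fuller plan would have to replace the stated method and not merely add detail.

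Four stronger readings are tempting and are not supported:

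- *No analysis uses any baseline variable.* Grip strength is adjusted for hand dominance, and grip strength and range of motion are corrected by the other side.
- *Frailty is collected and then left unused.* The Discussion gives it a purpose: to classify patients and learn whether frailty could inform later treatment decisions.
- *The standard errors are too large.* They are so only if type is prognostic. A marked distortion (7.9% too wide, type I error about 3.4%) needs a 15-point difference between types, more than the 11-point treatment effect for which the trial is sized.
- *The omission could decide the trial.* In the simulation, a 10-point type difference changes power by about one percentage point.

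For the binary and time-to-event outcomes, no loss has been quantified. The case there rests on consistency with the design.

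**Conclusion.** The point holds as a modest one. The article stratifies by AO/OTA type and then states comparisons of PRWE, complications, radiological success and return to work or sports that ignore it. If the types differ by 2 to 10 points in 52-week PRWE, and one type makes up 30% to 50% of patients, the unadjusted standard error is about 0.1% to 3.3% too large. At 10 points the type I error is about 4.2% (simulated) to 4.3% (formula). These differences and shares are assumptions, and if type is not prognostic the loss is zero. The error is conservative, there is no bias, and the sample size stands. The improvement is worth making because it is nearly free, not because the trial's conclusion is in doubt.

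**What to change.** - **Primary outcome:** analyse 52-week PRWE with a linear model containing treatment arm and AO/OTA type (A or C), reporting the adjusted mean difference with its 95% confidence interval.
- **Other continuous outcomes:** use the same model, including for the side-corrected grip strength and range of motion.
- **Complications and radiological success:** use a Mantel-Haenszel risk difference stratified by AO/OTA type.
- **Return to work and sports:** use a log-rank test stratified by AO/OTA type.
- **Optional, for efficiency:** add age and the Clinical Frailty Score to the PRWE model. Fix the covariates before outcomes are compared by arm, so that the choice cannot follow the results.

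The cost is wording only. AO/OTA type must be known for every patient in order to randomise, and demographics and frailty are already collected, so no new data, visits or patients are needed. The primary-analysis sentence has to be rewritten in any case, because a paired test does not fit two independent arms and conflicts with the two-sample test in the Sample size section. That is a separate fault, and the linear model would resolve it in the same edit.

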### Blinding

Due to the obvious differences between the two interventions, patients will not be blinded, nor will those who undertake radiological analysis. A blinded research assistant will undertake grip strength and ROM assessment at weeks six and 12.

### Follow-up assessments

All follow-up assessments will take place during follow-up visits initially with the treating consultant surgeon’s team. Radiographs, other diagnostic studies, and physiotherapy will be obtained/carried out as per standard care. The study will be reported in accordance with the principles outlines in the CONsolidated Standards of Reporting Trials (CONSORT) statement (Figure 2).^36^

**Fig. 2 F2:**
[figure not shown]
CONSORT flow diagram (with patient-reported outcome (PRO) extension) for the eFORRCE study. EQ-5D-3L, EuroQol five-dimension three-level questionnaire; MCD, minimal clinically important difference; PRWE, Patient-Rated Wrist Evaluation; QuickDASH, abbreviated version of the Arm, Shoulder And Hand questionnaire; VAS, visual analogue scale.

Follow-up assessments will be carried out for a year following injury (two, six, 12, and 26 weeks, and one year (52 weeks) post intervention). Routine follow-up in the study centre for patients who have sustained a distal radius fracture requiring operative intervention varies, but routinely outpatient clinic reviews with radiographs are at two, six, and possibly at 12 weeks. Patients will be asked to complete questionnaires by post or telephone at 26 and 52 weeks. Therefore, up to one additional visit with an additional radiograph will be required for this study (the 12-week visit), although face-to-face follow-up will continue beyond 12 weeks if clinically indicated, as would be the case in routine clinical care.

At each visit, physical examination, treatment, complications, and any reoperations for each patient will be assessed. A research assistant, blinded to the treatment method, will collect outcome scores and undertake functional testing/assessment. We also plan to send patients a further questionnaire and undertake a medical record review at two years to determine if they have undergone any further surgery on the affected wrist. During the consent process, patients will be asked if they consent to be contacted regarding any future longer-term analyses, which may be carried out separately.

